### Study description and study design

The StroCare intervention will be evaluated in a multi-center mixed-methods sequentially controlled intervention study with a longitudinal design (Fig. 1). Onset is acute inpatient stroke treatment with subsequent neurological rehabilitation. Patients will be enrolled during their initial stay at the stroke unit for the control and intervention group during a 12 months period each, starting with the control group. Afterwards, the intervention will be deployed and enrolment in the intervention group will start. For individual patients, the intervention will cover a period of 24 months. The intervention effects on outcomes will be evaluated by a quantitative survey 12 and 24 months after stroke. In terms of the implementation process, qualitative interviews will be conducted with patients after the implementation of the interventions. Additionally, employees (doctors, nurses, and IT staff) involved in the study will be interviewed before and after the implementation of the interventions. Comparative analyses of health-care costs are planned 6 and 12 months after admission with admitted permission to insurance data files. Enrolment of patients in the control group started in January 2020. Scheduled duration of the entire study from first-patient-in to last-patient-out has been extended from 24 to 36 months due to the COVID-19 pandemic.

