*Primary contact -* A study nurse of the department of Neurology of the UKE will contact the patient during primary acute stroke treatment. This nurse will be the responsible contact person for the patient for all medical questions for the next two years. The outpatient managed care will also be organised by the stroke nurse. Every three months for the following two years, the responsible stroke nurse maintains contact to the patient via telephone and every six months, arranges a consultation with the patient in the outpatient clinic including a check-up (ECG, blood samples) and a physical examination.*Outpatient managed care -* To achieve an well-structured outpatient care and to ensure regular follow-up appointments, the patients will be scheduled for a check-up and physical examination every six months at the respective acute clinic. The follow-up treatment will be performed by a study nurse and a neurologist experienced in stroke care and will comprise a neurological examination, carotid and intracranial ultrasound, evaluation of risk factors, and planning of further treatment.*Case Management -* In addition to establishing contact with a stroke nurse, each patient is assigned a case manager. The case manager acts on behalf of the health insurance company and the first contact is made during acute inpatient care. The case manager supports the patient regarding organisational issues, whereby the individual social situation is taken into account. In addition to care-relevant issues from the statutory health insurance system (like a request for classification of the degree of care), issues concerning the social nursing care insurance will also be addressed. The family, professional and financial situation, the housing situation and mobility factors, other health risk factors, and co-morbidities are taken into account by the case manager. Further non-medical context factors for patient-centered monitoring are, for example, existing responsibilities of the proxy and living wills, religious affiliation, private interests, and relevant biographical events. The Case Management should prevent disruptions between inpatient and outpatient care. It initiates and organizes seamless transitions.*Coverage of costs by the health insurance company -* By participating in StroCare, additionally to standard care costs are generated through study nurses, case manager, IT-portal, and neurological outpatient follow-up examinations in the UKE. These costs are paid by the insurance company as well as the standard care costs of neurological rehabilitation .*Electronical allocation of capacities (rehabilitation portal) -* Within StroCare an electronic rehabilitation portal will be implemented to speed up and secure a tailored referral to the five cooperating rehabilitation clinics. The portal is also meant to ensure efficient information transfer (medical reports, pictures, diagnostics) (see Fig. 2 for a comparison of the control and the intervention group).

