#### Standard care

Patients allocated to the control group experience the usual stroke care. After initial treatment at an acute clinic, a request for rehabilitation to the health insurance company has to be submitted and approved. Afterwards a suitable clinic for a neurological or geriatric rehabilitation with available capacities has to be found. This may not be achieved immediately after initial stroke treatment by the differently focused acute therapists, and in addition, not every patient receives the rehabilitation treatment best suitable for her/him [3].

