### Outcome measures

#### Effectiveness

In order to assess the effect of intervention, patient-reported outcomes will be surveyed measuring health-related quality of life (Fig. 3). They will be measured 12, and 24 months after baseline, using the questionnaire “Patient Reported Outcome Information System 10-Question Short Form” (PROMIS-10). The PROMIS-10 is a standardized questionnaire and consists of two scales measuring mental health and physical health [14], respectively, which will serve as the two primary outcomes. For evaluation of the PROMIS-10, at first a sum score and afterwards a t-score with standardized t-values is calculated. Reference of M ± SD= 50 ± 10 regards to a sample of healthy American subjects.

Additionally, the secondary outcome of depression and anxiety symptoms will be measured at all time points, using the “Patient Health Questionnaire-4” (PHQ-4) [15]. This questionnaire entails the two dimensions, depressive and anxiety symptoms, with two items each. The sum score ranges from 0 to 6 in each dimension. A score of 3 or higher indicates a potential anxiety or depression. The patient’s functional status will be assessed by the modified Rankin Scale questionnaire (smRSq) [16]. The scale of the smRSq ranges from 0 (“no symptoms”) to 6 (“death”). The outcomes of overall survival and stroke recurrence will be measured with the ICHOM-Standard set for Stroke [11]. The ICHOM-Standard Set for Stroke was developed under the coordination of the International Consortium for Health Outcomes Measurements (ICHOM) and measures a range of patient-reported outcomes from functionality to general health status. Further secondary outcomes are: utilization of health care services, patient’s waiting time between treatment phases, success in regaining target values of relevant risk factors (blood pressure, LDL-cholesterol, HbA1c) and costs. These parameters will be measured via the medical patient record and the rehabilitation portal. Also, a sociodemographic questionnaire will be used, measuring age, gender, living situation, partnership, vascular and non-vascular comorbidities.

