### Data analysis

#### Analysis of effectiveness outcomes

The structural equality of the control and intervention groups at baseline will be examined to detect imbalances, using descriptive statistical analysis.

In order to evaluate the intervention effect on the two primary outcomes at the 12-months follow-up, data will be analyzed using linear mixed models. In the fixed part of the model, exposure to the intervention (StroCare vs usual care) will be included as the independent variable of interest. Potential confounding variables will be added as fixed effects in case of baseline imbalance, including demographic characteristics, stroke type and severity of stroke symptoms, as well as vascular and systemic features. The random effects part of the model will include variance parameters for the intercept and for the treatment effect across the participating clinics, respectively. Findings regarding the primary outcomes with an alpha error rate below 0.025 will be considered statistically significant (Bonferroni adjustment for two outcomes).

The primary outcome at the 24-months follow-up and the secondary outcomes will be analyzed using similarly structured models. In the case that data are not normally distributed, generalized mixed models will be applied. Findings regarding the secondary outcomes with an alpha error rate below 0.05 will be considered statistically significant.

Parameter estimates will be reported with 95% confidence intervals. Missing values will be handled using multiple imputation.

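### Overall survival and stroke recurrence rest on a set described as patient-reported, while scheduled contact is much denser in the intervention group, so these two secondary comparisons risk detection bias against the programme

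*Protocol article*

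**What the plan says.** Under Outcome measures, Effectiveness, the protocol article names one source for these two secondary outcomes: "The outcomes of overall survival and stroke recurrence will be measured with the ICHOM-Standard set for Stroke". It says of this set that it "measures a range of patient-reported outcomes from functionality to general health status". The text as shown names no proxy, registry or claims source for death or recurrence.

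The timing of outcome assessment is in Study description and study design: "The intervention effects on outcomes will be evaluated by a quantitative survey 12 and 24 months after stroke". No difference between the groups is stated.

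Contact outside the survey does differ. Under StroCare intervention, "Every three months for the following two years, the responsible stroke nurse maintains contact to the patient via telephone", and "the patients will be scheduled for a check-up and physical examination every six months at the respective acute clinic". Each intervention patient also has a case manager acting for the insurer. Under Standard care, "Patients allocated to the control group experience the usual stroke care"; no scheduled study contact beyond the survey is described.

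Eligibility criteria make BARMER membership a condition of entry for everyone, for two reasons: the insurer bears the follow-up examination costs, and it gives access to patient data. The stated use of its files is limited: "Comparative analyses of health-care costs are planned 6 and 12 months after admission with admitted permission to insurance data files". Analysis of the economic outcomes also lists rehospitalizations among outcomes for which Cox or frailty models will be considered.

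On incomplete data, Analysis of effectiveness outcomes says only "Missing values will be handled using multiple imputation".

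**The concern.** Survival is an awkward outcome to take from a patient-reported set, since those with the event are the ones who cannot answer. Someone else has to supply the information, and how often someone is in touch then decides how many events are found.

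In the intervention group a nurse who rings every three months will normally learn of a death. A control's death between surveys may look like a form that was not returned. For recurrence the mechanism is weaker but runs the same way: six-monthly neurological follow-up may identify a mild event that the patient then knows of and reports, while a control with the same event may never have it recognised. The groups are also recruited one after the other, so response may differ by period as well.

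At stake are two secondary outcomes, each tested at 0.05. Fewer detected events among controls would make the programme look harmful, or would hide a real benefit. The simplified modified Rankin questionnaire scores death as its top grade, so an unknown death affects that secondary outcome too.

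**Working it through.** **The plan's own figures.** None is given for survival or recurrence. The only size calculation is for PROMIS-10: d = 0.3, power 80%, alpha 0.025. A two-sided two-sample t-test gives 212.5, so 213 per group, as stated. Adding 10% gives 213 × 1.10 = 234.3, so 235, as stated. (Dividing by 0.90 would give 237; that does not bear on this point.) These figures only supply the group sizes used below.

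**Contact over 24 months, side by side.**

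| | Intervention | Control |
|---|---|---|
| Outcome survey | 12 and 24 months | 12 and 24 months |
| Nurse calls | every 3 months | none described |
| Clinic visits | every 6 months | none described |
| Case manager | yes | no |

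The survey is the same as far as stated; the other opportunities to learn of an event are not.

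**Formula.** Observed risk = true risk × probability of detection. With equal true risks, the observed risk ratio (intervention/control) is the ratio of the detection probabilities.

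**Illustration 1. Assumptions, not in the article:** 6% die by 12 months in each group, all intervention deaths are found, and a share m of control deaths is missed. Expected deaths are 0.06 × 235 = 14.1 per group. The apparent risk ratio is 1/(1 − m).

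| m | Control deaths missed | Apparent risk ratio |
|---|---|---|
| 15% | 0.15 × 14.1 = 2.1 | 1/0.85 = 1.18 |
| 30% | 0.30 × 14.1 = 4.2 | 1/0.70 = 1.43 |
| 50% | 0.50 × 14.1 = 7.1 | 1/0.50 = 2.0 |

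The ratio does not depend on the 6%; the counts do.

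**Illustration 2. Assumptions, not in the article:** 95% detection in the intervention group, true event risk 5% to 15% in both groups, 213 per group, unpooled Wald test at two-sided 0.05.

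| Control detection | Observed ratio, true ratio 1 | Rejection rate, true ratio 1 | Observed ratio, true ratio 0.75 |
|---|---|---|---|
| 95% | 1.00 | 5% | 0.75 |
| 85% | 0.95/0.85 = 1.12 | 6% to 7% | 0.84 |
| 75% | 0.95/0.75 = 1.27 | 8% to 15% | 0.95 |
| 60% | 0.95/0.60 = 1.58 | 16% to 40% | 1.19 |

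The last column is 0.75 multiplied by the second. The first row shows that incomplete detection does no harm to the ratio if it is equal in both groups; only the difference matters.

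**Primary outcome, upper bound.** If 7 of 235 controls had died unnoticed and each imputed PROMIS-10 value were wrong by a full standard deviation, the control mean would move by 7/235 × 1 SD = 0.03 SD, against a planned effect of 0.3 SD.

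**The case against.** The strongest reply is that both groups get the same survey at the same times, and nothing says that the calls or visits supply these outcomes. The article's description of the ICHOM set is one general sentence, which does not exclude proxy, clinician or record items. Death is a codable grade on the Rankin questionnaire, so it need not appear as non-response. The outcome figure is not shown, and the tracing of vital status is detail that an article may leave to the full protocol. A living control can report a recurrence at 12 or 24 months. The detection rates above are invented, and even the extreme case of 14 against 7 deaths in 235 per group gives p of about 0.12 (Wald).

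Much of this stands, and it limits the point. Three stronger readings are tempting and are not supported:

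- A reader might infer that events will be detected unequally. The article shows unequal contact, not unequal detection, so this is a risk.
- A reader might infer that insurer data on death and recurrence are available for both groups to 24 months. The files are named only for costs at 6 and 12 months and subject to permission.
- A reader might infer that undetected control deaths, once imputed, bias PROMIS-10 in favour of the control group. The article does not say how known deaths are handled, so no direction follows. If known deaths were excluded, and the unnoticed dead controls were sicker at baseline and imputed accordingly, the control mean would fall, which favours the programme. The amount is at most about 0.03 SD on these assumptions.

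What the reply does not remove is that the article does name a source, describes it as patient-reported, and pairs it with contact that differs sharply by group. An identical form does not ensure equal detection when one group has many more occasions for an event to be noticed.

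**Conclusion.** The point holds as a risk to two secondary comparisons and should be acted on. The named source makes ascertainment of death and recurrence depend on contact, and contact is much denser in the intervention group, so any resulting bias would most likely count against the programme.

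Its size cannot be determined from the article. On the stated assumptions the false risk ratio runs from 1.12 (95% against 85% detection) to 2.0 (full against 50% detection), and a true ratio of 0.75 could appear as anything from 0.84 to 1.19. If detection is equal there is no bias. The figures concern missed events in general; nothing in the article lets recurrence be quantified separately from death.

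The PROMIS-10 sample size is not affected, and no bias of known direction in the primary analysis is shown.

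**What to change.** Name one source that is independent of group, on the same schedule for both groups: date of death and readmission for recurrent stroke from the BARMER files already planned for the 12-month cost analysis, extended to 24 months if permission allows. State the time horizon. Keep the survey answers as supporting data. Because admissions miss recurrences treated without a hospital stay, add a rule for those that is identical in both groups and does not draw on the nurse calls or the programme visits.

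Use the insurer's date of death to separate patients who have died from non-responders before any multiple imputation, and say how deaths enter each analysis.

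The cost is modest, since a request to the insurer is planned: additional fields and a longer window. The downsides are the delay with which insurer data arrive, censoring of patients who leave the insurer, and a possible need to extend the data permission. Whether death dates and 24-month data can be supplied should be checked with the insurer first, because the article does not show it.

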#### Analysis of the economic outcomes

We will employ both two-part (binomial, gamma) and generalized linear models (gamma distributed outcome) to analyze health care costs, because these models can incorporate the special features of cost distributions – i.e. right skewed distributions that contain a large proportion of zero values [20]. Cox-regression or frailty models as well as generalized linear models will be considered to analyze secondary outcomes such as rehospitalizations, the duration of hospital stays or the utilization of specific services.

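### Utilisation of health care services is measured from sources that StroCare itself feeds, so an outpatient or diagnostic count that includes programme contacts differs between groups partly by construction

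*Protocol article*

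**What the plan says.** Under Outcome measures, Effectiveness, the protocol article lists the outcome: "Further secondary outcomes are: utilization of health care services, patient’s waiting time between treatment phases", followed by risk-factor targets and costs. It then names the source for all of them: "These parameters will be measured via the medical patient record and the rehabilitation portal". Analysis of effectiveness outcomes puts the secondary outcomes through between-group models like those for the primary outcomes, with significance declared below 0.05.

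The StroCare intervention section makes scheduled care part of the intervention:

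- Clinic visits: "the patients will be scheduled for a check-up and physical examination every six months at the respective acute clinic".
- Tests arranged by the nurse: the stroke nurse "arranges a consultation with the patient in the outpatient clinic including a check-up (ECG, blood samples) and a physical examination".
- Content of the follow-up: it "will comprise a neurological examination, carotid and intracranial ultrasound, evaluation of risk factors, and planning of further treatment".
- Telephone contact: "Every three months for the following two years, the responsible stroke nurse maintains contact to the patient via telephone".

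The same section introduces the rehabilitation portal as a StroCare component. According to Study description and study design, the intervention is deployed after control enrolment. For the comparison group, Standard care says: "Patients allocated to the control group experience the usual stroke care".

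Analysis of the economic outcomes also plans models for "secondary outcomes such as rehospitalizations, the duration of hospital stays or the utilization of specific services". None of these sections says which services count as utilisation, or whether contacts created by the programme are among them.

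**The concern.** The outcome is meant to show what the programme does to patients' use of care. One of the two named sources is a medical record, and StroCare places visits, ECGs, blood samples and ultrasound examinations at the participating acute clinics, where such contacts would normally be recorded. The other source, the portal, is itself a StroCare component and does not exist for the earlier control group. The outcome and its stated sources together therefore observe the two groups unequally.

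Two misreadings are possible. A higher outpatient or diagnostic count under StroCare may show only that the schedule was delivered. Conversely, a real fall in other outpatient contacts may be cancelled by the scheduled ones. The article presents the programme as a reference model for other regions, so a utilisation result that cannot be interpreted would matter to payers and planners.

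**Working it through.** **The plan's own figure.** The article gives no sample size for utilisation, so the evaluable number for the primary outcomes is used. With d = 0.3, alpha 0.025 (two-sided assumed) and power 80%:

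n per group = 2 × (2.241 + 0.842)² / 0.3² ≈ 211.2, so 212 by the normal approximation. The t-test version gives 212.5, so 213. The stated 213 per group is reproduced.

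**Built-in surplus, from the schedule in the StroCare intervention section.** The nurse-arranged consultation and the six-monthly check-up are treated as one visit, the smaller count.

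- Visits: 12/6 = 2 by month 12; 24/6 = 4 by month 24.
- Nurse calls: 12/3 = 4 by month 12; 24/3 = 8 by month 24 (approximate).
- Controls: no scheduled programme contacts are described.

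**What the surplus does to a test.** Suppose all other use is identical in both groups and programme visits are counted. Then d = (surplus visits × attendance) / SD, z = d × √(213/2) = d × 10.32, and the probability of a significant result at two-sided 0.05 is about Φ(z − 1.96). The article gives no SD or attendance for contact counts, so both are assumptions. Calls are left out.

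| Horizon | Surplus | Attendance | Assumed SD | d | z | Probability of significance |
|---|---|---|---|---|---|---|
| 12 months | 2 | 100% | 4 | 0.50 | 5.16 | 99.9% |
| 12 months | 2 | 100% | 6 | 0.33 | 3.44 | 93% |
| 12 months | 2 | 100% | 8 | 0.25 | 2.58 | 73% |
| 12 months | 2 | 100% | 10 | 0.20 | 2.06 | 54% |
| 12 months | 1 | 50% | 4 | 0.25 | 2.58 | 73% |
| 12 months | 1 | 50% | 8 | 0.125 | 1.29 | 25% |
| 24 months | 4 | 100% | 8 | 0.50 | 5.16 | 99.9% |
| 24 months | 2 | 50% | 8 | 0.25 | 2.58 | 73% |

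The nominal rate is 5%, so the lowest row is still about five times nominal (25/5).

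**Masking.** At full attendance, if StroCare removed 1 other outpatient contact per patient by month 12, the total count would still show 2 − 1 = 1 more contact under StroCare. If it removed 2, the count would show no difference.

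**After the fix.** With programme contacts excluded from the count in both groups, the built-in surplus is 0.

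**The case against.** The strongest reply is that this is a condensed article. It names utilisation in a list without giving a unit, a count rule or service types, and the full protocol or analysis plan may already exclude programme contacts. The outcome-measures figure is not available either. This stands in part. A reader might infer from the text that programme contacts are counted in the outcome, but no section says so. A visit's presence in a record does not make it part of the outcome, and it is not stated that nurse calls are recorded there at all. The point is more than missing detail because the article does fix the outcome and its source, and that pairing favours ascertainment in the intervention group.

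A reader might also infer that all utilisation results are compromised, including admissions. The document does not support that. Analysis of the economic outcomes treats rehospitalisation, length of stay and use of specific services as separate outcomes, and scheduled outpatient check-ups do not inflate the first two.

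Nor does the arithmetic show that a significant difference is practically certain. The results depend on assumed SDs, on attendance and on every programme visit being additional. The Introduction describes usual aftercare by general physicians and neurologists, so some programme visits may replace visits that controls make elsewhere. The planned mixed models with a clinic-level random treatment effect would also change the probabilities.

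Finally, counting programme services is legitimate when resource use or cost is the question. That is correct; the difficulty arises only when the total is read as an effectiveness result.

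**Conclusion.** The concern holds for outpatient and diagnostic utilisation. If the count includes StroCare-scheduled contacts, the groups differ partly by construction: 2 visits per patient by month 12 and 4 by month 24 at full attendance, plus any nurse calls that are recorded. With 213 per group, two-sided 0.05 and no effect on other care, 2 extra visits give a 93%, 73% or 54% chance of significance at an SD of 6, 8 or 10. Those figures rest on assumed SDs, full attendance, no substitution and a simple two-group normal approximation. The chance is smaller with poorer attendance or with substitution. They illustrate the size of the problem and do not forecast the result.

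The inference that the clinic visits enter the medical record is close, because they take place at the participating acute clinics, but it remains an inference. The primary PROMIS-10 outcomes, rehospitalisation and length of stay are untouched. One secondary outcome should be redefined before the data are analysed.

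**What to change.** 1. Define the between-group utilisation outcome as services other than StroCare-scheduled visits, tests and calls, and list it by service type.
2. Take it for both groups from one source equally available to both. The insurer files already planned for the cost analyses at 6 and 12 months fit, because every participant is insured with the participating insurer.
3. Flag programme items in those files. The insurer pays for the programme services, so they may appear there too, and changing the source alone would not remove the surplus.
4. Report total utilisation, including programme contacts, descriptively, and keep it for the cost analysis.

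The cost is a revised outcome definition and a flag for programme items, with no added burden on patients. The article ties the insurer files to 6 and 12 months, so comparing utilisation at 24 months would need data access to be extended.
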